### Participant adherence

A member of the site study team will be responsible for data collection at the various time points within the trial. Predominantly the research nurses will be involved in coordinating data collection activities and ensure compliance with appointments. Following surgery a 1 week follow up appointment will be booked for participants in the treatment arm before they leave the hospital. At subsequent follow up time points (2, 3, 6, 9 and 12 months) where possible an appointment for the next time point will be scheduled in. The research nurse will telephone the participant 1 week before the appointment as a reminder where resource allows.

### Withdrawal

Participants are free to withdraw from treatment or the trial at any time. If a participant wishes to withdraw they will be able to speak to a member of the site study team i.e. respiratory or neurology consultants or the research nurse. This will be documented on a participant withdrawal form. Any data already collected during the course of the trial up to the point of withdrawal will be used in the final analysis. We will ask the participant for their permission to continue to collect safety (i.e. adverse event) data and data on survival.

Participants will have three options for study withdrawal: withdraw from treatment but remain within the study (all trial data would continue to be collected at subsequent follow up time points as per protocol); withdraw from study and unless the patient objects, any data collected up to this point would be retained and used in the study analysis and a final survival check will be performed; withdraw from study entirely. Unless the patient objects, any data collected up to this point would be retained and used in the study analysis. If the patient does not wish to be contacted with regard to safety or survival, no further contact relating to the study will be made.

### Qualitative interviews

The qualitative component will draw directly upon both patient and carer’s own experience and views, within the context of everyday lives [20,21]. An essential part of DiPALS is not only to demonstrate the efficacy of DP but also to ensure that any extension of life is not to the detriment of quality of life. The qualitative component will complement the data collected by SF36 and SAQLI for this purpose. The qualitative component will provide information not easily obtained from questionnaires that will facilitate the implementation of respiratory care pathways incorporating Diaphragm pacing should the study demonstrate benefit.

### Design

A total of 12 patients and 12 carers will be recruited for the qualitative component from those allocated to treatment across all sites. Although eligibility of participants for the main study will have been determined through screening for the trial those selected for interview will reflect the diversity of the MND population. This will involve purposively selecting patients to reflect the variation within the predefined patient prognostic factors. It is anticipated that MND patients will not be able to tolerate an interview in addition to follow up assessments at local sites therefore an experienced research fellow will conduct the interviews at a time and location that is convenient for participants.

Ideally the patients and carers will be interviewed separately because they may have different views but joint interviews will be undertaken if requested by the participants. The research team are experienced in working with MND patients and appreciate the need for sensitivity whilst conducting the qualitative interviews with these vulnerable participants.

### Conduct

The in-depth interviews will be undertaken with DP patients 1 and 6 months post implantation. The first interview at 1 month will focus on the intervention and the practicalities of having the implant fitted and adjusting to life using the device. This information will be essential to inform the clinical team of issues related to both understanding the procedure including use of the equipment and any beneficial or adverse impact it may have.

A second interview will be undertaken at approximately 6 months post implantation. This will focus on the impact the intervention has had on QoL. Changes to QoL are reported to occur within this timeframe for all MND patients. Six months is also considered an appropriate time to allow patients receiving DP (and caregivers) to become familiar with the intervention and its impact on QoL. Interviews will provide an opportunity to take account of their views and experience of the intervention.

### Analysis

Data from the 48 qualitative interviews will be recorded, transcribed and undergo Framework analysis [22]. Although Framework analysis was developed for applied policy it has proved useful in applied health research. Analysis will be ongoing and iterative involving concurrent data collection and analysis, with systematic efforts to check and refine developing categories of data. Themes identified in the early phases of data collection will inform the areas of investigation in later interviews. The emerging analysis will be discussed at regular team meetings to identify recurring themes within the data which will explore respondents’ underlying reasoning, discuss deviant cases and reach agreement on recurrent themes and findings.

### Data collection

Once participants have been enrolled and allocated their treatment the data collection process starts (Table 1). Data collection occurs at baseline, 2, 3, 6, 9 and 12 months for both groups. Additionally the DP group will undergo data collection at the time of surgery and 1 week following surgery. The subgroup of 12 participants and carers who will be undertaking the qualitative sub study will also undergo interviews at 1 and 6 months post implantation.

**Table 1 T1:** Data collection

**Data collection tool**	**Time point of study**	**When collected/given to patient**	**By who**	**Purpose**
Informed consent form	Recruitment	In clinic, face to face	Neurology or respiratory consultant	Ensure participants have been consented appropriately
Screening and eligibility assessment form	Recruitment/Screening	In clinic	Neurology or respiratory consultant or research nurse	Ensure protocol violations or deviations are avoided. Include ECG, blood gases, blood test, FVC and phrenic nerve evaluation tests
ALSFRSr	Screening	As above	As above	Allows minimisation on bulbar function
Survival	1 week, 2, 3, 6, 9, 12 months, then finally at last follow up for last patient	In clinic, telephone	Research nurse	Primary outcome measure
*EQ5D questionnaire (patient and carer)	Screening, 2, 3, 6, 9 and 12 months	In clinic or over the phone	Neurology or respiratory consultant or research nurse	QALYs, secondary outcome measure
SF36	Screening, 2, 3, 6 and 12 months	As above	As above	Generic quality of life, secondary outcome measure
Sleep Apnoea Quality of Life (SAQLI)	Screening, 2, 3, 6 and 12 months	As above	As above	Respiratory specific quality of life, secondary outcome measure
*Caregiver Burden Inventory questionnaire	Screening, 2, 3, 6 and 12 months	As above	As above	Secondary outcome measure
Side effects/ adverse event/concomitant medications and devices forms	All time points as required	As above	As above	AE/SAEs
Healthcare resource use	2, 3, 6, 9 and 12 months	As above	As above	Economic, secondary outcome measure
Patient Diary incorporating:	1 week, 2, 3, 6, 9 and 12 months	In clinic, at hospital or at home	Neurology or respiratory consultant and Patient and Carer	Main outcome Record DP and NIV use
* NIV use				
* DP use and				
* DP Parameters setting				
NIV use	Screening	As above	As above	Main outcome
Medical history and examination on CRF	Screening and 12 months	In clinic	Neurology or respiratory consultant	Eligibility for trial, safety
Surgery evaluation form/ pre op safety check	Screening, Surgery and 1 week	In clinic or hospital	Neurology or respiratory consultant or Surgeon	Safety and eligibility for surgery
Surgical implantation/ intra operative form	Surgery	In hospital	Neurology consultant or Surgeon	Testing DP device in situ
Discharge evaluation form	Surgery	In hospital	Neurology or respiratory consultant or surgeon	Demonstrate patient and carer competent to use and care for DP device
DP parameters setting	Surgery	Clinic	Neurology or respiratory consultant	Evaluate the DP device, allow optimal use of device
*Qualitative interview (n = 12, Patient and carer)	1 and 6 months post implantation	Participants place of choice	Qualitative fellow	Sub study outcome

### Trial database - prospect

Prospect is a CTRU online Database system. Users are able to perform data entry remotely via their secure account, access to which is restricted by use of an individual username and password. The study manager, data managers, PI’s, co-investigators, research nurses and administrators will have access to relevant anonymised data. Data input will be the responsibility of the research nurses. The system has a full electronic audit trail and will be regularly backed up. The secure data management system will incorporate quality control procedures to validate the study data. Error reports will be generated where data clarification is needed. Data quality will be the responsibility of the Sheffield CTRU Trial Manager and the Data Management Team.

### Data handling and confidentiality

Detailed data management and data quality issues will be set out in a data management and monitoring plan. Data will be collected and retained in accordance with the Data Protection Act 1998. Anonymised trial data will be entered onto a validated database system designed to an agreed specification between the Chief Investigator and Sheffield CTRU. Output for analysis will be generated in a format and at intervals to be agreed between Sheffield CTRU and the Chief Investigator. Trial documents will be retained in a secure location during and after the trial has finished.

All source documents will be retained for a period of at least 5 years following the end of the trial. Where trial related information is documented in medical records those records will be retained for at least 5 years after the last patient last visit.

Monitoring and audit by the relevant health authorities will be permitted by the sponsor. These include the Research Ethics Committee and local R&D departments. The sponsor will be allowed to monitor and audit the trial at each site and be allowed access to source data and documents for these purposes.

### Adverse events

All adverse events will be reported in accordance with the CTRU Adverse Event and Serious Adverse Events (SAE) SOP (PM004) which incorporate the Medicines for Human Use (Clinical Trials) Regulations 2004 (SI 2004/1031) definitions. All trial participants will be encouraged to contact and inform their site research team if they experience any of the medical problems outlined under SAE’s or relevant AE’s included (above). Those that are not picked up through general contact will be identified at follow up visits. A member of the site study team will enquire about any adverse events since the previous visit and record these on the adverse event paper CRF and database. For any SAEs a paper and database entry will be completed. The event will be assessed by the local Principal Investigator and the form will be kept in the site file. SAEs will be reported in the periodic safety reports to the research ethics committee. Standard or expected disease progression is an SAE exclusion. Adverse events which must be reported include chest infection requiring the use of antibiotics, infection at the DP site or a revision of the DP device.

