## Abstract

**Background:**

Motor neurone disease (MND) is a devastating illness which leads to muscle weakness and death, usually within 2-3 years of symptom onset. Respiratory insufficiency is a common cause of morbidity, particularly in later stages of MND and respiratory complications are the leading cause of mortality in MND patients. Non Invasive Ventilation (NIV) is the current standard therapy to manage respiratory insufficiency. Some MND patients however do not tolerate NIV due to a number of issues including mask interface problems and claustrophobia. In those that do tolerate NIV, eventually respiratory muscle weakness will progress to a point at which intermittent/overnight NIV is ineffective. The NeuRx RA/4 Diaphragm Pacing System was originally developed for patients with respiratory insufficiency and diaphragm paralysis secondary to stable high spinal cord injuries. The DiPALS study will assess the effect of diaphragm pacing (DP) when used to treat patients with MND and respiratory insufficiency.

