### Safety and tolerability of DP

A total of 350 implantations in Spinal Cord Injured patients and MND patients have taken place [14]. Generally implantation surgery is well tolerated. Detailed safety data has been published on 51 patients with MND who have undergone the implantation procedure (49 in the FDA trial or pilot and 2 compassionate use cases). In the trial/series the FVC at implantation ranged from 45%-89%, whereas the compassionate cases had an FVC of 26% and 28%. All patients were extubated without difficulty and there was no 0 day or 30 day mortality [17].

Within the HDE approval submission safety analysis was performed on the HUD subgroup (n = 86). There were no reports of serious unanticipated adverse device effects and no reports of any serious adverse effects related to the patients’ use of the device following discharge. There were 3 reports of serious adverse events (3.5%) related to implantation. These were pneumothorax (n = 2) requiring intervention and respiratory failure following surgical complications (n = 1) [14]. These were previously recognised risks of laparoscopic procedures.

Discomfort from pacing was reported in 22 patients (26%). This was described as mild in 20 patients and severe in 2 patients. Resolution was achieved in most cases by adjusting the stimulation parameters.

Mild to moderate infection at the percutaneous exit site was reported (n = 9, 9.3%). These were treated with antibiotics. In two cases the subcutaneous wires needed to be repositioned under local anaesthetic.

No serious adverse events occurred as a result of malfunctioning device components. The following malfunctions were reported; anode breaks (n = 18,21%), anode falling out of body (n = 6,7%), external electrode breaks (n = 28, 33%), broken stimulators (n = 6, 7%) and broken stimulator cables (n = 4, 5%) [14]. In practical terms in MND, malfunctioning components resulted in a loss or diminution of conditioning therapy until the malfunction was corrected. Design improvements have subsequently been implemented in an effort to improve reliability and to simplify malfunction resolution.

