### Secondary research objectives

The secondary objectives of this trial will be to evaluate the effect of Diaphragm Pacing (DP) on:

Quality adjusted life years (QALYs), as calculated by combining EQ-5D and mortality data [18]. The objective of the health economic analysis will be to assess the cost-effectiveness of DP compared to standard care in patients with ALS/MND. A cost-utility analysis will be undertaken using the costs, EQ-5D and mortality data from the trial. This will be supplemented with decision analytic modelling to estimate lifetime cost-effectiveness for the patient cohort recruited to the trial.

Quality of life of the patient, as assessed by the sleep apnoea quality of life index (SAQLI), SF-36 [6,9] and qualitative interviews.

Quality of life of the main carer of the patient, as assessed by the Caregiver Burden Inventory [19] and qualitative interviews.

For each efficacy endpoint, the treatment effect will be assessed by analysing the difference between groups over the 12-month follow-up period, and the difference at 12 months.

The trial will also assess the safety and tolerability of DP. Study endpoints safety (adverse events) and tolerability (patient withdrawal from treatment) will be assessed at each time point over the course of the trial. Please refer to Figure 1: Trial overview.

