### Trial oversight

Three committees have been established to oversee the conduct of the study: Trial Management Group (TMG), Trial Steering Committee (TSC) and Data Monitoring and Ethics Committee (DMEC). All committees are governed by Sheffield CTRU standard operating procedures. The TMG consists of the Chief and Principal Investigators and key staff within the CTRU. The role of the TMG is to implement all parts of the trial and to act on the recommendations from the TSC and DMEC.

The TSC consists of the Chief Investigator, key staff within the CTRU (as non voting members), an independent chair and three independent members. The roles of the TSC are to provide supervision of the protocol and statistical analysis plan, provide advice on and monitor progress of the trial, to review information from other sources and to consider recommendations from the DMEC. The DMEC consists of an independent chair and 2 independent members including a statistician. The DMEC has responsibility for monitoring the results provided by the trial statistician to the plan described in the trial protocol with reference to efficacy and safety, reviewing information from other sources, providing recommendations to the TSC on why the trial might be modified or discontinued in terms of ethics and safety and considering adverse events. There are no planned interim analyses for the trial.

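### The SAE exclusion for disease progression can take non-fatal respiratory deterioration out of the between-arm safety comparison, possibly to a different degree in each arm

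*Protocol article*

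**What the plan says.** All places are in the protocol article.

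- **Adverse events.** The general rule is "All adverse events will be reported in accordance with the CTRU Adverse Event and Serious Adverse Events (SAE) SOP (PM004"), an SOP that is not shown. Site staff ask about events since the last visit and record them. For SAEs, "The event will be assessed by the local Principal Investigator". The section then states without qualification: "Standard or expected disease progression is an SAE exclusion". It goes on: "Adverse events which must be reported include chest infection requiring the use of antibiotics, infection at the DP site or a revision of the DP" (that is, of the pacing hardware). SAEs go into the periodic safety reports to the ethics committee.
- **Secondary research objectives.** "The trial will also assess the safety and tolerability of DP". The safety endpoint is adverse events at each time point. The Data analysis section compares proportions of patients with adverse outcomes.
- **Abstract, Background.** "respiratory complications are the leading cause of mortality in MND patients".
- **Safety and tolerability of DP.** Three serious implantation-related events are listed from earlier data: two pneumothoraces and "respiratory failure following surgical complications (n = 1").
- **Data collection, Table 1.** Survival is collected from 1 week to 12 months and again at the last patient's last follow-up. FVC and blood gases appear only on the screening form.
- **Trial oversight.** The DMEC monitors efficacy and safety and considers adverse events. "There are no planned interim analyses for the trial".

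**The concern.** An exclusion for expected progression is workable when progression looks different from the harm the treatment could do. Here the two overlap. The disease produces worsening respiratory weakness, chest infections and respiratory failure. The intervention is abdominal laparoscopy under general anaesthesia followed by stimulation of the diaphragm, so breathing is also where harm would most plausibly show.

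A complication in the days after surgery would probably be recognised for what it is. A respiratory admission some weeks later, or a faster decline during pacing, carries no mark that separates it from the natural course in one patient. Only a comparison of all such events between arms can answer the question, and the exclusion acts before that comparison is made.

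The judgement is also made with knowledge of allocation. The site team randomises, participants are told their arm, and only one arm has surgery, with no sham procedure described. The article describes no blinded or central review of events. At stake is whether the serious-event part of a stated safety objective gives a fair comparison.

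**Working it through.** **1. Which events can the rule remove?**

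| Event | Effect of the exclusion |
|---|---|
| Death | None on the primary comparison: overall survival counts every death from randomisation, with no judgement on cause |
| Chest infection needing antibiotics | None: named as reportable |
| DP-site infection, device revision | None: named as reportable, but possible only in the DP arm |
| Respiratory failure soon after surgery | Probably none: not disease progression on its face, and counted as implantation-related in earlier data |
| Later non-fatal respiratory failure, or admission for respiratory decline | May be classed as progression and not counted as an SAE |

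The exposure is the last row.

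**2. What does the filter do to the comparison?** Let p_DP and p_C be the fractions of such events classed as progression in each arm. Then

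observed SAE ratio = true ratio × (1 − p_DP) / (1 − p_C).

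If p_DP = p_C, the ratio is unchanged and only counts, hence precision, are lost. If they differ, the ratio is biased. With assessors aware of allocation the direction is open. Ready attribution to the disease in the DP arm would hide harm; heightened vigilance after surgery would exaggerate it. The article gives neither fraction, nor any event rate for non-fatal respiratory failure, so no number can be put on this.

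**3. Could the primary outcome reveal harm alone?** First, the plan's sample size (Statistics, Sample size). Inputs: control survival 45%, 20% and 10% at minimum, average and maximum follow-up; hazard ratio (HR) 0.45; 85% power; two-sided 5%; 10% loss.

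- Control event probability by Simpson's rule: 1 − (0.45 + 4×0.20 + 0.10)/6 = 0.775.
- DP event probability, with each survival value raised to the power 0.45: 0.501.
- Mean: 0.638.
- The Freedman formula needs 63 events: 63/0.638 = 98.7 patients, and 98.7 × 1.1 = 108.6 (or 98.7/0.9 = 109.7). This agrees with the stated 108.

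Now reverse the direction. Evaluable patients are 108 × 0.9 = 97.2. For a harmful HR h (my assumption), the DP event probability is 1 − (0.45^h + 4×0.20^h + 0.10^h)/6. Deaths D are 97.2 times the mean of that and 0.775. Power is Φ(√D × ln h / 2 − 1.96), the Schoenfeld form.

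| Assumed HR, DP v control | Expected deaths | Power to show harm |
|---|---|---|
| 1.25 | 78.5 | 16.6% |
| 1.50 | 80.7 | 44.5% |
| 1.75 | 82.2 | 71.8% |
| 2.00 | 83.2 | 88.5% |
| 2.22 (= 1/0.45) | 83.9 | 95.5% |

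These are approximate. At the design HR of 0.45 with 97.2 patients, Schoenfeld gives 88.2% and Freedman 84.8%. The pattern is clear: large excess mortality would be seen, moderate excess probably would not reach significance.

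**4. Do other data fill the gap?** Table 1 schedules no FVC or blood gases after screening. NIV use is recorded, but less need for NIV is an anticipated benefit of DP, so a change in it is not a clean harm signal. The respiratory quality-of-life score (SAQLI) is indirect. Resource-use forms may record admissions, but the article assigns them to the economic evaluation, not to a by-arm respiratory safety table.

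**The case against.** The other side has substantial points, and most of them stand.

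- **A reader might infer that the trial cannot detect respiratory harm from DP.** The documents do not support that. All deaths enter a two-sided primary comparison, with good power against a doubling of the hazard. Counts of expected deaths therefore do not measure what this rule could lose.
- **A reader might infer that the DMEC would be blind to harm.** Having no planned interim analysis does not mean the DMEC is denied deaths by arm; its remit covers efficacy and safety.
- **A reader might infer that only chest infection can be compared between arms.** The list of reportable events is introduced as inclusive, not exhaustive, and the section opens by covering all adverse events.
- **The exclusion is from SAEs.** The article does not say progression events go unrecorded as ordinary adverse events, and the safety endpoint is not limited to SAEs. That stands, but a respiratory failure logged as non-serious would still be missing from the serious-event comparison.
- **Definitions sit in an SOP that is not shown, and an article condenses.** The boundary of expected progression may be drawn there. For that reason the missing definition is not the finding. The finding is the rule that the article does state, which carries no exception for respiratory events or admissions.

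**Conclusion.** The concern holds in a limited form. Applied as printed, the exclusion lets non-fatal respiratory failure and respiratory admissions be classed as progression by assessors who know the allocation, so the between-arm SAE comparison may be depleted and may be biased in either direction. The safety assessment is weakened and open to bias; it is not unable to detect harm.

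Size: no effect on the primary outcome, sample size or type I error. The number of non-fatal events affected is unknown. The gap matters most for moderate harm, where survival alone has about 16.6% to 44.5% power (assumed HR 1.25 to 1.5).

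Assumptions: the trial is open, inferred from the randomisation and surgery sections; the unseen SOP does not already carve respiratory events out of the exclusion; the power figures use the plan's control survival, its 10% loss and illustrative harmful HRs. Severity: moderate.

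**What to change.** Replace the exclusion sentence in the Adverse events section with a rule of this content:

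- Deaths, and all hospital admissions or prolonged stays for respiratory failure or respiratory deterioration, are recorded as SAEs in both arms whatever the presumed cause. They may be exempt from expedited reporting.
- These events are tabulated by arm as randomised.
- The by-arm counts go into the DMEC safety reports, without a formal efficacy test, so no alpha is spent.

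The cost is one protocol change, some extra forms, and a higher headline SAE count in both arms that the report will need to explain. The change should be prospective, because SAE forms never completed cannot be reliably reconstructed later.
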